### Recruitment

Each patient referring to our center for CCS management is observed and tested for diagnostic angiography indications. On average, in our center, 100–200 CCS patients undergo PCI monthly. In addition to the relatively large number of patients referred to our clinic, they typically come from a high socioeconomic background, which helps ensure better compliance and adherence to the prescribed medications.

### Randomization (sequence generation, concealment, implementation)

Participants will be randomly allocated to either the control group or the experimental group in a 1:1 ratio using permuted block randomization through a web-based randomization service (https://www.sealedenvelope.com/randomisation/simulation/). Allocation concealment will be ensured as the randomization service will not be accessed by the interventional cardiologist until the patient has been recruited into the trial. Recruitment occurs after diagnostic angiography and before stent insertion. The only person who is involved in randomization is the interventional cardiologist who conducts PCI.

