### Intervention

An interventional cardiologist will perform angiography under the supervision of a senior interventional cardiologist. CCS patients who require revascularization based on the newest guideline [21] will undergo PCI using DES. FFR (Fractional Flow Reserve) ≤ 0.8 or iFR (Instantaneous Wave-Free Ratio) ≤ 0.89 will be considered as evidence of ischemia. PCI will be performed using the radial or femoral approach to achieve complete revascularization of at least one stenosis. All target lesions will be revascularized using the 4th generation DES. Randomization will take place after diagnostic angiography but before stent insertion (Fig 1). Eligible patients will be divided into two groups: the control group, which will get conventional DAPT with aspirin and Clopidogrel (80 mg aspirin once daily, and 75 mg clopidogrel once daily), and the experimental group, which will receive ticagrelor monotherapy (90 mg twice daily) following PCI for six months. Antiplatelet therapy will start before or at the time of PCI. Patients will receive a loading dose of assigned drugs (325 mg for aspirin, 300 mg for clopidogrel, and 180 mg for ticagrelor) before stent insertion unless they are already on pre-PCI maintenance therapy with the mentioned drugs. Peri-procedural aspirin use will not be allowed in the experimental arm.

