### Blinding

The allocation of patients to each group is known only to the cardiologist responsible for randomization. This cardiologist is not involved in the patient’s treatment, follow-up, outcome assessment, or data analysis to ensure blinding of the physician team to the allocation. The allocation is stored using a code number in a computer-based data system, which will remain blinded until the analysis is complete. Neither the patients, investigators, nor data analysts will be aware of the group assignment. To ensure the blinding of participants and prevent them from identifying their assigned treatment group, despite differences in the type and number of medications, a standardized method of tablet administration was employed. Following randomization and prior to stent insertion, all patients will receive two unmarked tablets as a loading dose. In the control group, patients will be administered one 325 mg aspirin tablet and one 300 mg clopidogrel tablet. In contrast, patients in the intervention group will receive two 90 mg ticagrelor tablets, administered by the cardiologist responsible for the randomization process. For the maintenance dose, each patient will be provided with two boxes of tablets and instructed to take one tablet from each box daily, one in the morning (8:00 AM) and one in the evening (8:00 PM). In the intervention group, both boxes will contain 90 mg ticagrelor tablets, whereas in the control group, one box will contain 80 mg ASA tablets and the other will contain 75 mg clopidogrel tablets. The same cardiologist responsible for randomization will also distribute the medication boxes containing the required drugs for the six-month follow-up period. This approach is designed to preserve the double-blind nature of the study, ensuring that participants, physicians, outcome assessors, and other study personnel remain unaware of group allocations. In the event of adverse reactions or if a medication switch is deemed necessary by the DSMB or TMC, the group allocation will be unblinded, and appropriate adjustments will be made.

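### The protocol makes the PCI operator the sole randomiser, yet says the randomiser takes no part in treatment and that physicians are blinded; these statements cannot all hold

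*Protocol article*

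**What the plan says.** Two sections of the Protocol article assign the randomising role.

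- Randomization (sequence generation, concealment, implementation): "The only person who is involved in randomization is the interventional cardiologist who conducts PCI". On access: "the randomization service will not be accessed by the interventional cardiologist until the patient has been recruited into the trial".
- Blinding: "The allocation of patients to each group is known only to the cardiologist responsible for randomization". It continues: "This cardiologist is not involved in the patient’s treatment, follow-up, outcome assessment, or data analysis".

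The Blinding section then gives this person two tasks with study drug. The ticagrelor loading dose is described as "two 90 mg ticagrelor tablets, administered by the cardiologist responsible for the randomization process", and the same cardiologist distributes the boxes for six months. The section concludes that participants, physicians, assessors and other staff do not know the allocation.

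Timing is fixed in the Intervention section: "Randomization will take place after diagnostic angiography but before stent insertion". The Abstract, Objective, and Study design and setting sections call the trial double-blinded without qualification.

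**The concern.** The conflict is about who knows the arm once allocation has been made. It is not about whether the next allocation can be predicted.

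PCI is the index treatment. A person who performs it is involved in treating the patient, so the Randomization and Blinding sections cannot both describe one cardiologist. The Blinding section also conflicts with itself, because giving and dispensing study drug is part of treatment.

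Two steps would be exposed if the operator knows the arm.

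- **Procedural choices.** The Intervention section aims for complete revascularization of at least one stenosis. Some discretion remains over further lesions, stents and optimisation of the result. These choices bear on stent thrombosis, MI and repeat revascularization, all of which are in the primary composite.
- **The PCI exclusion.** The eligibility criteria exclude unsuccessful PCI and PCI without optimal stent placement. This can only be judged after stenting, hence after randomisation. If the judgement depends on the arm, it can undo the balance that the allocation-based intention-to-treat analysis relies on.

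**Working it through.** The point concerns the text, so the check sets the statements side by side.

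1. **Who randomises?** The operator and nobody else (Randomization).
2. **When?** After diagnostic angiography and before stent insertion (Intervention, Randomization, Participant timeline).
3. **Who knows the arm?** The randomiser only (Blinding).
4. **What does the randomiser not do?** Treatment, follow-up, outcome assessment, analysis (Blinding).
5. **What does the randomiser do?** Gives loading tablets, stated for the intervention group, and distributes the six-month boxes (Blinding).
6. **Who is said to be blinded?** Physicians among others (Blinding).

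Statements 1, 2 and 3 together mean that the operator knows the arm before implanting the stent. That contradicts 4 and 6. Statement 5 contradicts 4 even if 1 is set aside.

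There are three ways to read the text.

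- **The Randomization section governs.** The operator is unblinded at the index procedure, and the claim in 6 fails for that role.
- **The Blinding section governs.** The randomiser is someone other than the operator, and the operator may be blinded. Statement 1 is then wrong.
- **Treatment in statement 4 means care after PCI.** The operator is unblinded and the follow-up team blinded. The text does not say this, and supplying six months of study drug is itself care after PCI, so 5 still conflicts with 4.

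The documents do not say which reading was used.

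**Figures.** None depends on this point. The stated 2424 per arm reproduces from Formula 1 with p = 0.02, margin 0.01, one-sided alpha 5% and power 80%: 2 × ((1.645 + 0.842)/0.01)² × 0.02 × 0.98 ≈ 2424. It is unaffected.

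**Can a bias be sized?** Only by assumption. Take true rates of 3% (ticagrelor, at the margin) and 2% (control). Apply a Wald one-sided 95% limit against 1%, with exact binomial enumeration, and suppose operator behaviour changes ticagrelor-arm events by a fixed share. The 5% and 10% shares are illustrative and come from no document. The chance of declaring non-inferiority is then:

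| Assumed change in ticagrelor events | 2,424 per arm | 180 per arm |
|---|---|---|
| none (3.00%) | 5.2% | 5.3% |
| 5% fewer (2.85%) | 9.9% | 6.3% |
| 10% fewer (2.70%) | 17.3% | 7.6% |
| 5% more (3.15%) | 2.5% | 4.4% |
| 10% more (3.30%) | 1.1% | 3.7% |

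The sign of the effect follows entirely from the assumed direction, and its size from the assumed share and the sample size. The table shows why no magnitude is attached to this point.

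**The case against.** The strongest reply is that this is a slip in describing roles and that the consequences are easily overdrawn. Much of that stands.

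- **A reader might infer that the operator is unblinded in every index procedure.** That holds only if the Randomization section governs. Under the Blinding section it need not be true of any procedure.
- **A reader might infer an inflated risk of a false non-inferiority claim.** The documents support neither the size nor the direction. More care in the aspirin-free arm would favour ticagrelor, whereas stopping sooner could leave lesions untreated and count against it.
- **A reader might infer that the operator also records complications or later judges the need for revascularization.** No section assigns either task to the operator, and the Blinding section keeps the randomiser out of follow-up and outcome assessment.
- **Safeguards exist.** The Data monitoring, harm, and auditing section has significant MACE determined by a committee that does not know the assignments. The Intervention section ties revascularization to the guideline and to FFR and iFR thresholds, under senior supervision, with one generation of stent. This narrows the operator's discretion without removing it.
- **The PCI exclusion belongs to the supervising cardiologist.** The text does not say whether that person is the operator or learns the arm, so influence is possible but not shown.

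The reply does not remove the contradiction. This is not detail that an article leaves to a fuller document: the article states who randomises, when, and who is blinded, and the statements conflict. Blinded review of MACE comes too late to correct procedural choices or exclusions that depended on the arm.

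**Conclusion.** The contradiction is established from the text alone and rests on no numerical assumption. The stated blinding of physicians cannot hold for the operator if the Randomization section is followed, and the stated exclusion of the randomiser from treatment fails on the Blinding section's own account of drug handling.

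The scope is limited to the operator's role, the procedural choices left after randomisation, and possibly the PCI exclusion. The size and direction of any bias cannot be derived. It would go too far to conclude that the double blind as a whole has failed: nothing here shows that patients, follow-up staff, outcome assessors or analysts learn the arm by this route.

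The point still needs correcting because protection from bias depends on these roles and the correction is cheap. According to Trial status, recruitment began on August 1, 2024 and was expected to end by December 1, 2024. Patients have therefore been enrolled under one arrangement or another, and the reader cannot tell which.

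**What to change.** Amend the Randomization and Blinding sections so that they name the same role. The person who opens the randomisation service and handles study drug should be a named team role that does not perform or supervise that patient's PCI, does not decide the exclusion for unsuccessful or suboptimal PCI, and does not follow the patient.

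If this is not done, state in the Abstract, in Study design and setting, and in Blinding that the PCI operator is unblinded, and limit the double-blind claim to the roles that are in fact blinded.

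In either case, report which arrangement was used for patients already enrolled, and settle the matter before any continuation beyond the initial phase of 360.

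Coded, pre-packed kits are another route, but a further conflict must be reconciled first. The Intervention section exempts patients already on maintenance therapy with the drugs from the loading dose, while the Blinding section gives every patient two loading tablets. Under the exemption, whether a tablet is due can depend on the arm, so someone who cannot see the arm could not apply it from a sealed kit.

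The cost is a change of wording plus minor cath-lab logistics, or, if the operator stays unblinded, a less favourable description of the blinding. Kits would add packing work and might come too late for the initial phase.

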### Blinding

The allocation of patients to each group is known only to the cardiologist responsible for randomization. This cardiologist is not involved in the patient’s treatment, follow-up, outcome assessment, or data analysis to ensure blinding of the physician team to the allocation. The allocation is stored using a code number in a computer-based data system, which will remain blinded until the analysis is complete. Neither the patients, investigators, nor data analysts will be aware of the group assignment. To ensure the blinding of participants and prevent them from identifying their assigned treatment group, despite differences in the type and number of medications, a standardized method of tablet administration was employed. Following randomization and prior to stent insertion, all patients will receive two unmarked tablets as a loading dose. In the control group, patients will be administered one 325 mg aspirin tablet and one 300 mg clopidogrel tablet. In contrast, patients in the intervention group will receive two 90 mg ticagrelor tablets, administered by the cardiologist responsible for the randomization process. For the maintenance dose, each patient will be provided with two boxes of tablets and instructed to take one tablet from each box daily, one in the morning (8:00 AM) and one in the evening (8:00 PM). In the intervention group, both boxes will contain 90 mg ticagrelor tablets, whereas in the control group, one box will contain 80 mg ASA tablets and the other will contain 75 mg clopidogrel tablets. The same cardiologist responsible for randomization will also distribute the medication boxes containing the required drugs for the six-month follow-up period. This approach is designed to preserve the double-blind nature of the study, ensuring that participants, physicians, outcome assessors, and other study personnel remain unaware of group allocations. In the event of adverse reactions or if a medication switch is deemed necessary by the DSMB or TMC, the group allocation will be unblinded, and appropriate adjustments will be made.

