Given that a substantial number of patients with CCS may already be on aspirin or P2Y12 inhibitors, and to enhance the applicability of the study to real-world clinical practice for this population, prior use of these agents was not included in the exclusion criteria. However, in such cases, any ongoing aspirin or P2Y12 inhibitor therapy will be discontinued upon enrollment, and the allocated study treatment will be initiated according to the assigned group protocol.

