### Participant timeline

After a clear decision to conduct diagnostic angiography for CCS patients based on current guidelines [22,23]. They will be informed about the study and available options. After providing the informed consent, the pre-PCI questionnaire will be completed by an interventional cardiologist and a member of TMC. Patients will be randomized to treatment or control group after diagnostic angiography and before stent insertion. The loading dose of the assigned medications for each group will be administered to the patient prior to stent insertion. After the procedure, the enrolled patients will be visited for evaluation and management of underlying diseases, routine assessments, and optimal medical therapy. Clinical follow-ups will be performed at 1, 3, 6, and 12 months and telephone contacts will be performed every month till the end of the study. An assessment of angina status, cardiovascular drug use, dyspnea, and any serious adverse events will be recorded during these clinical follow-up visits. Illustrative participant timeline is shown in Figs 1 and 2.

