### Data monitoring, harm, and auditing

Prior to conducting statistical analysis, an expert from the cardiology department, who is not part of the research team, will review and validate all measurements. This adjudicator will examine the quality of each measurement and will omit any that do not meet the required standards, treating them as missing data in the analysis. Additionally, an impartial safety committee, working without knowledge of the treatment assignments, will review and determine any significant MACE. After this adjudication process is finalized, the database will be made accessible for data analysts. The study’s executive committee will communicate any adverse events to a separate DSMB. This board, which operates independently, holds the power to halt the trial prematurely in cases where patient safety is at risk or the main research goal is achieved. If the adverse event rate (primary safety and efficacy endpoint) in the intervention group surpasses that of the control group by more than 20% during any interim analysis, the DSMB will review the data and may recommend termination of the trial if necessary. The DSMB will be responsible for regular safety monitoring, including unexpected serious adverse events, mortality, and severe bleeding, with safety reports generated for review. Additionally, all MACE and bleeding events will be promptly reported to the DSMB, which will conduct independent audits each month. In addition to tracking MACE and bleeding, we will systematically collect data on other potential harms, such as drug reactions, dyspnea, and adverse events, through both spontaneous reporting and structured follow-up visits. Adverse events will be recorded, analyzed, and reported using Common Terminology Criteria for Adverse Events version 4.0 (CTCAE v4.0). All harms, regardless of their frequency, will be reported in publications to provide a comprehensive view of the safety profile. This approach ensures transparency and provides a detailed understanding of the potential risks associated with the interventions.

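### The Intervention section waives the loading dose for patients already taking the listed drugs, but the Blinding section gives every patient two active loading tablets; for prior users both rules cannot hold

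*Protocol article*

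**What the plan says.** Four sections of the Protocol article bear on the loading dose.

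- **Intervention.** "Patients will receive a loading dose of assigned drugs" (325 mg aspirin, 300 mg clopidogrel, 180 mg ticagrelor) "before stent insertion unless they are already on pre-PCI maintenance therapy with the mentioned drugs". The same section states that "Antiplatelet therapy will start before or at the time of PCI" and bars peri-procedural aspirin in the ticagrelor arm.
- **Blinding.** "all patients will receive two unmarked tablets as a loading dose". The contents are named: one 325 mg aspirin and one 300 mg clopidogrel tablet in the control arm, two 90 mg ticagrelor tablets in the other. The stated purpose is "To ensure the blinding of participants and prevent them from identifying their assigned treatment group".
- **Participant timeline.** "The loading dose of the assigned medications for each group will be administered to the patient prior to stent insertion". No exception is given.
- **Participants and eligibility criteria.** "prior use of these agents was not included in the exclusion criteria". Earlier aspirin or P2Y12 therapy is stopped at enrolment and the allocated treatment begins. The authors expect a substantial number of such patients but give no percentage.

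**The concern.** For a patient who arrives on aspirin, clopidogrel or ticagrelor, the Intervention section may call for no load, or only part of one, where the Blinding section calls for two active tablets. Such patients are eligible and expected, so the conflict will arise in practice.

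Two things are at stake. The first is participant blinding: the Blinding section relies on an equal number of unmarked tablets because the arms use different drugs, and a waiver that works differently by arm removes that equality at the loading step. The second is peri-procedural dosing: on one reading of the waiver, some patients in the aspirin-free arm would be stented without the ticagrelor load.

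**Working it through.** No stated figure needs reproducing. The check compares the rules and counts tablets.

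**Inputs.** Two loading tablets per arm with the named contents (Blinding; 2 × 90 mg = 180 mg of ticagrelor, matching the Intervention section). Waiver for prior users (Intervention). Prior users eligible (Participants and eligibility criteria).

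**Step 1: can both rules hold?** The Blinding rule covers all patients and names active contents. Any waived dose therefore departs from it, however the waiver is read. Stopping earlier therapy at enrolment does not settle the matter, because that sentence says only that the allocated treatment then starts according to the group's protocol, and the loading rule in that protocol is the point in dispute.

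**Step 2: waiver read drug by drug, no replacement tablets.** The Intervention section speaks of a load of the assigned drugs, so the natural reading is that an assigned drug already being taken is skipped. Let A, C and T be 1 for prior aspirin, clopidogrel and ticagrelor, and 0 otherwise.

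- Control tablets = 2 − A − C
- Ticagrelor-arm tablets = 2 × (1 − T)

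| Prior therapy | Control | Ticagrelor arm |
|---|---|---|
| None | 2 | 2 |
| Aspirin | 1 | 2 |
| Clopidogrel | 1 | 2 |
| Aspirin + clopidogrel | 0 | 2 |
| Ticagrelor | 2 | 0 |
| Aspirin + ticagrelor | 1 | 0 |

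The count differs between arms for every type of prior user shown.

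**Step 3: waiver read as any listed drug cancelling all loading.** Every prior user takes 0 vs 0, so the count gives nothing away. It still contradicts the Blinding section. A prior aspirin or clopidogrel user assigned to ticagrelor would start ticagrelor by the time of PCI, but without the 180 mg load and with peri-procedural aspirin barred.

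**Step 4: the Blinding rule read literally.** Everyone takes 2 vs 2 and the count is balanced. Prior users are then loaded again with drugs they already take, which may add bleeding in a trial whose primary safety endpoint is BARC type 3 or 5 bleeding.

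**Step 5: waiver with dummies.** Control: (2 − A − C) active + (A + C) dummy = 2. Ticagrelor arm: 2(1 − T) active + 2T dummy = 2. The count is 2 vs 2 for every row of the table.

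**The case against.** The best defence is that this is a rule and its exception. The Intervention section sets the dosing and states the exception; the timeline and Blinding sections restate loading for other purposes without repeating it. Whether a skipped tablet is replaced by a dummy is the kind of detail an article leaves to the full protocol. That argument stands in part: unequal counts follow only if the waiver works drug by drug and no dummy is used, and the full protocol may describe one. It does not remove the contradiction, because the Blinding section says all patients and lists active drug as the contents. A dummy would itself depart from that text.

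A reader might infer that the blind is broken for prior users. The documents do not support that. A patient would have to know the waiver rule to draw anything from the count, and nothing says that patients are told it. The loading step is a single moment, after which both arms follow the same two-box schedule for six months. The tablets are handed out by the cardiologist responsible for randomization, who already knows the allocation and is said to take no part in follow-up or outcome assessment. A committee "working without knowledge of the treatment assignments, will review and determine any significant MACE".

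A reader might also infer that staff will apply different rules and so blur the planned subgroup by prior use. With one role giving the load at a single centre, that is speculation.

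Finally, the missed ticagrelor load rests on the less natural reading of the waiver. It is a reason to word the rule clearly, not evidence that patients went without the load.

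**Conclusion.** The plan is wrong as written: it gives two incompatible instructions for one step in patients it expects to enrol, and nothing in the article decides between them. This holds on every reading of the waiver.

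The consequences are conditional. Unequal tablet counts need the drug-by-drug reading and no replacement tablets; even then, inferring the arm is possible for some prior users, not certain. The missed 180 mg load needs the any-drug reading. If the Blinding rule governs, blinding at this step is intact, but prior users are reloaded.

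The share of prior users is not given, so the number affected among the 360 initiation-phase patients cannot be derived, nor can any effect on the endpoints. The point is limited to the loading step. It merits correction because the conflict touches both a stated blinding method and a peri-procedural dose, and the correction is cheap.

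**What to change.** For any continuing phase, state one rule in the Intervention, Participant timeline and Blinding sections:

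- every patient takes two loading tablets;
- the waiver applies only to an assigned drug that the patient already takes;
- each skipped tablet is replaced by a matching dummy;
- every patient new to ticagrelor who is assigned to that arm receives the 180 mg load.

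The cost is a wording change and a small supply of dummy tablets, one or two for each patient with a waived dose. The total cannot be fixed without the share of prior users.

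Deleting the waiver would also balance the counts without dummies, but it trades a wording problem for reloading prior users. That is a clinical decision and not a simple correction.

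Initiation-phase recruitment was due to end on December 1, 2024, so for those patients the remedy is to clarify which rule was followed and report the loading actually given, by arm and by prior use.
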